**Fig. 1 Fig1:**
[figure not shown]
Study variables and collection time points. GHQ-12 12-item version of the General Health Questionnaire

The hypotheses of this study are the following:IG participants, as compared to CG participants, will demonstrate higher rates of biochemically verified 7-day point prevalence smoking abstinence, at all evaluation time points (48 h and 1, 6, and 12 months post discharge).IG participants, as compared to CG participants, will experience longer periods of sustained abstinence as demonstrated by sequential biochemically verified 7-day point prevalence smoking abstinence, at all evaluation time points.IG participants who continue to smoke, as compared to CG participants, will show greater reduction in the number of cigarettes smoked per day, at all evaluation time points.IG participants who continue to smoke, as compared to CG participants, will show an increase in the progression of their readiness to quit smoking, based on stages of change, at all evaluation time points.IG participants, as compared to CG participants, will have a higher level of self-efficacy to quit at all evaluation time points.

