##### Secondary outcome measure

We will also record other smoking variables such as continuous abstinence. Moreover, for nonabstinent patients we will ask about their tobacco use (quantity), type of tobacco consumed (cigarette/cigar/other), number of quit attempts, and other variables included in the “smoking” section in Fig. 1. Moreover, using an ad-hoc Likert scale from 0 to 10 we will evaluate the level of self-efficacy to quit or reduce consumption, the intention to quit, and the intention to reduce consumption. The individual’s willingness to quit will be also evaluated according to the Prochaska and Di Clemente Stages of Change model, which measures four stages of readiness to quit smoking (precontemplation, contemplation, action, and maintenance) [43].

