### Procedure

The research team designed a telephone-based intervention with a proactive approach to help patients quit smoking after discharge from hospitals. The intervention will take into account the recommendations made by a group of experts in the design of telephone-based interventions (quitlines) aimed at patients with mental illnesses [39]. The intervention will also be based on the protocol of the general quitline of 061 CatSalut Respon and a clinical intervention guide for smoking cessation in patients with mental disorders [28]. Depending on the case, the intervention will be directed to: increase motivation to quit; achieve abstinence; prevent relapses if achieving abstinence; reduce consumption and increase motivation to quit smoking when the patient is still not ready or motivated to quit; and/or recommend pharmacological treatment.

The intervention will be conducted by 061 CatSalut Respon nurses within the first 48 h, 1 week, 15 days, and 1, 3, 6, 9, and 12 months after discharge. IG subjects will be contacted by the trained nurses and will provide an intervention strategy adapted to each patient situation in each call (whether they smoke, take pharmacological treatment to quit, are ready for a quitting day calls, “D day”, etc.) according to an algorithm procedure (Fig. 1). The first telephone call at 48 h will serve as a starting point for the quitline intervention outside the hospital and to take baseline data post discharge.

CG subjects will be contacted after the first 48 h following discharge by nonclinical telephone assistants who will provide brief advice (only in the first call) and collect data for comparison, at this time (48 h), 1, 6, and 12 months post discharge. The investigators trained the nonclinical telephone assistants in order to conduct the interviews in a neutral tone following the wording of each of the questions and not giving health recommendations, as they are not qualified to do so. For patients who express their desire to quit, telephone assistants suggest they talk with their outpatient clinic doctor, nurse, or psychologist to receive aid*.*

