**Fig. 3 Fig3:**
[figure not shown]
Strategy intervention in the intervention group. NRT nicotine replacement therapy

All patients in the intervention group will receive eight telephone calls during 1 year (48 h, 1 week, 15 days, and 1 , 3 , 6 , 9, and 12 months post discharge), regardless of whether they continue smoking or not. The intervention lasts for 12 months, unless the patient rejects to continue participating in the study. The intervention adapts its objectives depending on the smoking status of the patient in each call (see Fig. 3 in which the different strategies are explained according to the smoking status assessed in each call, whether he/she is abstinent or not, is willing to allocate a “D day”, takes NRT).

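### The stages-of-change scale named for hypothesis 4 has no stage for a smoker who is ready to quit, so it can miss part of the motivational effect among continuing smokers

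*Protocol article*

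**What the plan says.** The fourth hypothesis, in the list that closes the Background, reads: "IG participants who continue to smoke, as compared to CG participants, will show an increase in the progression of their readiness to quit smoking", and this is to be judged "based on stages of change, at all evaluation time points". Those time points are 48 h and 1, 6 and 12 months after discharge. The population is therefore continuing smokers and the instrument is the stage model.

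The section Secondary outcome measure describes that instrument as one "which measures four stages of readiness to quit smoking (precontemplation, contemplation, action, and maintenance". It names nothing between contemplation and action and defines none of the four stages; it only cites a source for the model.

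The same section also plans 0-10 ratings: "we will evaluate the level of self-efficacy to quit or reduce consumption, the intention to quit, and the intention to reduce consumption". For patients who are not abstinent it lists "number of quit attempts, and other variables included in the" smoking section of Fig. 1.

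On the intervention, Procedure gives as one aim "reduce consumption and increase motivation to quit smoking when the patient is still not ready or motivated to quit". Telephone-based intervention components says that the strategy in each call depends on the patient's status, including "whether he/she is abstinent or not, is willing to allocate a “D day”, takes NRT".

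**The concern.** Hypothesis 4 keeps only people who still smoke and then measures them on a scale whose upper half, on the ordinary meaning of the words, belongs to people who have stopped. That leaves two usable levels and one step between them. A contemplator is at the top of the usable range. If that person goes on to act, he or she has stopped and leaves the population of the hypothesis. If he or she becomes ready for a quit day but still smokes, the stage does not change.

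This readiness is a state on which the intervention calls branch. A real gain among contemplators could therefore leave no trace in the stage result, and a flat result could be misread as no motivational effect. Readiness among smokers matters here because the trial enrols patients whatever their motivation, and the planning rates in Sample size and randomization imply that most will still smoke at 12 months: 100% - 20% = 80% in the intervention group and 100% - 5% = 95% in the control group.

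**Working it through.** The plan gives no figure for this hypothesis, so there is none to reproduce. The check is a comparison of passages and a count of the possible moves.

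**Inputs**
- Population: participants who continue to smoke (hypothesis 4, Background).
- Scale: four named stages (Secondary outcome measure).
- A pre-quit state recognised by the intervention: readiness or willingness to set a quit day (Procedure; Telephone-based intervention components).
- Assumption, not in the article: action and maintenance mean that the person has already stopped.
- Assumption, not in the article: c, the share of continuing smokers who were in contemplation at baseline. No stage distribution is given, so c is shown as a range.

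**Possible moves for someone who still smokes**

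| Stage at baseline | Later state, still smoking | Change in stage |
|---|---|---|
| Precontemplation | Thinking about quitting | Up one |
| Contemplation | Ready to set a quit day | None; no such stage is named |
| Contemplation | Action | Not possible while smoking, under the assumption |

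**Share able to register a gain**

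Only those who start in precontemplation can move up, so the share is 1 - c.

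| c | 1 - c |
|---|---|
| 20% | 80% |
| 40% | 60% |
| 60% | 40% |
| 70% | 30% |

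These are upper limits on who can show progress, not estimates of who will. If true upward movement were spread evenly over baseline stages, the difference between arms on the stage scale would shrink by the same factor, 1 - c. The article supports neither an even spread nor any rate of movement, so I do not turn this into percentage points.

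**Would whole-arm analysis cure it?** No. If quitters were included, action and maintenance would largely restate the abstinence result, and the step just before quitting would still be unnamed.

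**The case against.** Four points can be made on the other side.

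1. *The stages are undefined.* The article calls all four stages of readiness. If action also covers smokers who are making changes or attempts, the ceiling does not arise. This stands: a reader might infer as fact that only two stages are open to a smoker, but the documents do not settle it. Even under the assumption the limit is not absolute. The primary outcome requires 7 days of abstinence verified by carbon monoxide, so someone who stopped three days ago could be classed as non-abstinent and still report being in action.

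2. *The trial measures motivation in other ways.* A reader might infer that the step the intervention aims at goes unrecorded, or that the trial cannot show a motivational effect. The documents contradict this. The 0-10 intention score and quit attempts are recorded, the specific objectives compare motivation and quit attempts between groups, and Data analysis includes motivation among the outcomes. The aim for patients not yet ready is also partly captured by the move from precontemplation to contemplation. What remains is that hypothesis 4 itself is tied to the stages only.

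3. *The ceiling may be modest.* The limitations in the Discussion say that highly motivated patients are excluded, which points to a lower c. That is fair. Even so, at c = 20% a fifth of continuing smokers could show no gain.

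4. *Figs. 1 and 3 are not shown.* They may carry item wording or a quit-day field. That could soften the point, but the text is explicit about the number and names of the stages.

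**Conclusion.** The point holds in a limited form. Hypothesis 4 rests on a stage measure with no category for a smoker who is ready to quit, while a 0-10 score with the needed range is planned but not linked to it. Assuming that action and maintenance mean already stopped, the stage result can respond only to moves out of precontemplation, and at most 1 - c of continuing smokers can contribute: 80% down to 30% for c from 20% to 70%, a range assumed for illustration. The stage result is thus insensitive to part of the motivational effect. It does not follow that the trial as a whole is blind to that effect. The hypothesis is secondary; the primary outcome, its analysis and the sample size are untouched. This is a low-priority improvement.

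**What to change.** Assess hypothesis 4 on the 0-10 intention-to-quit score already planned, as change from the first value recorded before any counselling, and report the stages alongside. The text does not show whether this item is asked before discharge. If the first value comes from the 48 h call, it should be taken before advice is given in either arm; change can then be assessed only at 1, 6 and 12 months.

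In addition or instead, add one answer option to the stage item for a smoker who intends to quit soon, worded and asked identically in both arms. It should not be defined by having set a quit day with the quitline, because that is a step in the intervention group's calls and would score process as outcome.

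State what each stage means, and report action and maintenance with the abstinence results.

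The cost is rewording one hypothesis and, if the option is added, a slightly longer item, with no extra visits or staff. The drawback is that the 0-10 scale is ad hoc, which is a reason to keep the stages beside it.

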#### Independent variables

Using a data collection form we will collect the following information:Sociodemographic data such as sex, age, occupation, and highest level of education attained.History and pattern of tobacco use, which will include information to obtain the Heavy Smoking Index as a measure of nicotine dependence self-reported by the participants [44, 45].General health data, such as self-perceived general health assessment by the question “how would you describe your health in a general way?”, and other medical conditions.Mental health data, such as diagnoses according to the DSM-5 groups of diagnostic criteria [46] and psychotropic treatment, will be obtained from participants’ clinical records by the researchers, whereas information about the number of emergency room visits, readmissions to psychiatric wards, and evaluation of mental distress measured using the 12-item version of the General Health Questionnaire (GHQ-12) [47, 48] will be self-reported by the participants.Variables of smoking cessation services reported by the participants, such as, if used, any other strategy for tobacco cessation, will be registered. It will also be recorded whether the patient has actively spoken with their psychiatrist, psychologist, nurse, or family doctor about their participation in the quitline, whether the professionals have agreed, and whether they have helped them, to assess the possible influence of these variables on the success (or failure) of the intervention.

Collected variables and their collection frequency are detailed in Fig. 1.

### Procedure

The research team designed a telephone-based intervention with a proactive approach to help patients quit smoking after discharge from hospitals. The intervention will take into account the recommendations made by a group of experts in the design of telephone-based interventions (quitlines) aimed at patients with mental illnesses [39]. The intervention will also be based on the protocol of the general quitline of 061 CatSalut Respon and a clinical intervention guide for smoking cessation in patients with mental disorders [28]. Depending on the case, the intervention will be directed to: increase motivation to quit; achieve abstinence; prevent relapses if achieving abstinence; reduce consumption and increase motivation to quit smoking when the patient is still not ready or motivated to quit; and/or recommend pharmacological treatment.

The intervention will be conducted by 061 CatSalut Respon nurses within the first 48 h, 1 week, 15 days, and 1, 3, 6, 9, and 12 months after discharge. IG subjects will be contacted by the trained nurses and will provide an intervention strategy adapted to each patient situation in each call (whether they smoke, take pharmacological treatment to quit, are ready for a quitting day calls, “D day”, etc.) according to an algorithm procedure (Fig. 1). The first telephone call at 48 h will serve as a starting point for the quitline intervention outside the hospital and to take baseline data post discharge.

CG subjects will be contacted after the first 48 h following discharge by nonclinical telephone assistants who will provide brief advice (only in the first call) and collect data for comparison, at this time (48 h), 1, 6, and 12 months post discharge. The investigators trained the nonclinical telephone assistants in order to conduct the interviews in a neutral tone following the wording of each of the questions and not giving health recommendations, as they are not qualified to do so. For patients who express their desire to quit, telephone assistants suggest they talk with their outpatient clinic doctor, nurse, or psychologist to receive aid*.*

For those patients who met the criteria, clinicians will invite them to participate and will deliver an informative leaflet of the study (Additional file 1). Informed consent will be requested within 24 h before discharge (see Fig. 2, recruiting process). Clinicians will register participants’ data in a software program that will be used for randomization and to transfer this information to 061 CatSalut Respon to contact the participants. All of this baseline information is registered in the software during the hospital stay. Finally, on the day of discharge the subjects are automatically assigned randomly to one of the two groups (IG or CG) by the software. The study is blinded to prevent professionals from the hospital, and patients, from knowing to which group they have been assigned.

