### Variables

#### Outcome measures

##### Primary outcome measure

Self-reported 7-day point prevalence smoking abstinence, biochemically verified with expired carbon monoxide (CO) measures, is the primary outcome. Seven days of abstinence has been chosen as a consumption measure [41]. This variable will be recorded in every call of the intervention (48 h, 1 week, 15 days, and 1, 3, 6, and 12 months post discharge). Abstinent subjects at 1, 6, and 12 months in either of both groups (IG or CG) will be invited to attend a consultation at their hospital to verify their abstinence through the detection of exhaled carbon monoxide. The abstinence rate between the IG and the CG will be compared at 1, 6, and 12 months. In each call, nicotine withdrawal symptoms will be assessed according to the scale proposed by Hughes and Hatsukami [42].

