### Telephone-based intervention components

The intervention is based on cognitive-behavioral therapy. The intervention will include components based on Bandura’s social learning theory, social cognitive theory [49], and the transtheoretical model of change [43]. This theory allows evaluating the patient motivation phase and adapting the interventions according to each phase [27].

These components are included in the training curriculum aimed at 15 nurses from 061 CatSalut Respon who will deal with patients with mental disorders from the IG. The specific training will include the definition and description of the most common mental disorders, symptoms, usual treatments, warning signs, and management, as well as the peculiarities of the smoking cessation treatment in these patients (Table 1).

**Table 1 Tab1:** Components of the formative curriculum

• Mental disorders, symptomatology, and general treatment	
• Content, extension, and frequency of the proactive calls	
• Withdrawal syndrome assessment in the mental health context	
• Pharmacological recommendations about nicotine replacement therapy	
• Peculiarities of smoking cessation treatment in patients with mental disorders, alert signs, and management	
• Motivational intervention	
• Communication strategies	

Trained nurses will help those patients to identify their barriers and opportunities to achieve abstinence. They will also help them to set objectives, strategies to tackle “craving”, positive reinforcement toward progress, and increase their self-efficacy. If necessary, nurses will recommend NRT according to the protocol of a clinical guideline [28], as it is a medication that does not require medical prescription in Spain. Nurses will have a written protocol and an algorithm to deliver the intervention strategy according to each patient’s situation (Fig. 3). Nurses will recommend the patients inform their psychiatrist and/or psychologist that they are receiving this telephone-based intervention to quit smoking.

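### Who asks about smoking differs by arm (counselling nurses in the intervention group, neutral nonclinical assistants in the control group), so assessor is confounded with treatment, chiefly for the self-reported outcomes

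*Protocol article*

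**What the plan says.** *Intervention group (IG).* The Procedure section states: "The intervention will be conducted by 061 CatSalut Respon nurses". It adds: "IG subjects will be contacted by the trained nurses and will provide an intervention strategy adapted to each patient situation in each call". The 48 h call both starts the counselling and takes the post-discharge baseline. Under Primary outcome measure, of 7-day abstinence: "This variable will be recorded in every call of the intervention"; seven times are then listed, without 9 months. The text on the intervention components says: "All patients in the intervention group will receive eight telephone calls during 1 year". It includes 9 months and has smoking status assessed at each call.

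*Control group (CG).* The Procedure section states: "CG subjects will be contacted after the first 48 h following discharge by nonclinical telephone assistants who will provide brief advice". The advice is confined to the first call, and data are collected at 48 h and 1, 6 and 12 months. The assistants are trained to "conduct the interviews in a neutral tone following the wording of each of the questions".

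*Verification.* Patients of either arm who report abstinence at 1, 6 or 12 months are invited to their hospital for an exhaled CO test.

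*Blinding.* The Procedure section says: "The study is blinded to prevent professionals from the hospital, and patients, from knowing to which group they have been assigned". Callers are not mentioned. The section on intervention components says: "Nurses will recommend the patients inform their psychiatrist and/or psychologist that they are receiving this telephone-based intervention to quit smoking".

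**The concern.** An outcome that depends on a patient's answer should be asked in the same way in both arms. Here the IG patient answers the nurse who has been counselling them, in the call where counselling is given. The CG patient answers someone with no therapeutic role who reads set questions. A difference in reported cigarettes, quit attempts, readiness or self-efficacy could then reflect the intervention, the relationship with the caller, or both, and the analysis cannot separate them. The plan evidently saw the value of neutral, fixed-wording questioning, but describes it for CG only.

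Frequency of contact is a second possible difference. Quit attempts and duration of abstinence look back over an interval, so comparing the arms on the same date does not by itself equalise how they were ascertained.

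At stake is the interpretation of the secondary comparisons and of the 48 h comparison. The primary comparison at 1, 6 and 12 months is at stake to a lesser degree.

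**Working it through.** **1. The calls side by side.**

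| | IG | CG |
|---|---|---|
| Caller | Nurses delivering the intervention | Nonclinical assistants |
| Counselling in the call | Every call | Brief advice, first call only |
| Fixed wording, neutral tone | Not described | Stated |
| Calls | 48 h, 1 week, 15 days, 1, 3, 6, 9, 12 months = 8 | 48 h, 1, 6, 12 months = 4 |
| Recordings listed for the primary variable | 7 (no 9 months) | Not listed separately |
| CO test | 1, 6, 12 months, if abstinence is reported | Same |

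The stated eight calls are reproduced by the count. Shared times are 48 h and 1, 6 and 12 months, so 8 − 4 = 4 calls are IG-only (7 − 4 = 3 recordings on the shorter list).

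**2. Longest interval between recordings.** CG: 12 − 6 = 6 months. IG: 3 months if the 9-month call records the outcome (3 to 6, 6 to 9, 9 to 12), but 12 − 6 = 6 months on the seven-time list. The document supports both readings, so a shorter longest gap in IG is not established.

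**3. Which outcomes have an objective check.** The Background lists five hypotheses, each at all evaluation times:

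- 7-day abstinence: called biochemically verified at 48 h and 1, 6 and 12 months, but CO testing is scheduled only at 1, 6 and 12 months. The 48 h comparison therefore rests on self-report.
- Sustained abstinence: defined by sequential verified abstinence, so checked wherever CO is scheduled.
- Cigarettes per day, readiness, self-efficacy: no check stated.

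Three of the five hypotheses thus rest on self-report alone, and one more does so at 48 h. Quit attempts, named in the specific objectives, also have no check.

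**4. Who asks the secondary items in IG.** The text says directly only that abstinence or smoking status is recorded in the nurse calls. For the other items this is an inference: the nurse call is the only IG telephone contact described at the shared times, and no separate assessor appears. How often each item is asked is left to Fig. 1, which was not visible in the text reviewed.

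**5. Size.** The document gives no figure for a reporting difference between callers. As an illustration only, take a purely self-reported abstinence outcome with true abstinence of 5% in both arms, and 134 CG and 267 IG patients evaluable (167 × 0.8 = 133.6; 334 × 0.8 = 267.2). Let IG reports be inflated by e. The chance of a significant result favouring IG is Φ((e − 1.96·s0)/s1), with s0 the pooled and s1 the unpooled standard error. For e = 0.02 the pooled rate is (134 × 0.05 + 267 × 0.07)/401 = 0.0633, s0 = 0.0258, s1 = 0.0245, and Φ(−1.25) ≈ 0.11. For e = 0.03 it is 0.18 and for e = 0.05 it is 0.39, against a nominal 0.025. Every e is an assumption. The illustration fits neither the CO-verified primary outcome nor the 48 h rate, which the document does not give. It shows only that small reporting differences can matter when nothing is verified.

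**The case against.** The best defence has four parts.

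First, the primary outcome is CO-tested in both arms at the patient's hospital, so a false claim made to a friendly nurse goes on to a test. This largely stands. For the caller to bias the verified result, true abstainers would have to report or attend differently by arm. That is possible, since the caller's question is the gate to an invitation, but the document gives no evidence of it.

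Second, comparisons are set at times common to both arms, and extra calls are part of the treatment in a pragmatic trial. This stands for point-prevalence outcomes. It does not settle outcomes that look back over an interval.

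Third, a condensed article need not print the nurses' script, and one application holds both arms' data. The nurses may have a fixed form. Even so, the different callers, and recording within counselling calls, are stated rather than omitted.

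Fourth, the blinding sentence never claims that callers are blinded. That is correct.

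A reader might infer more than the text supports:

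- *That every secondary outcome is unverified.* Sustained abstinence is defined through verified abstinence.
- *That quit attempts are asked more often in IG.* That depends on Fig. 1.
- *That blinding is broken.* The nurses' advice threatens it only if patients follow it and the clinician told is among the hospital staff meant to be blinded. Such conversations are to be recorded.
- *That the planned 15-point effect is overstated by some number of points.* No inflation figure is given, and more frequent questioning can reveal relapses as well as quit attempts, so even the net direction is open.

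**Conclusion.** The concern holds in a limited form. Assessor is confounded with arm by the stated design. The exposure is mainly in cigarettes per day, quit attempts, readiness, self-efficacy and abstinence at 48 h, where a verified comparison is hypothesised but no CO test is scheduled. The primary outcome at 1, 6 and 12 months is exposed only through who reports abstinence and who attends testing. Contacts are eight against four (seven listed recordings in IG); whether this makes ascertainment of quit attempts and duration unequal depends on Fig. 1. Neither size nor net direction of bias can be derived from the document.

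This rests on two assumptions: that the secondary items in IG are asked in the nurse calls, and that no shared questionnaire exists outside the article. If Fig. 1 or the full protocol shows otherwise, the point shrinks accordingly. It is worth correcting because the correction is cheap, but it does not undermine the primary comparison.

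**What to change.** - Use one fixed-wording outcome questionnaire in both arms at 48 h and 1, 6 and 12 months. In IG it is asked and saved before any counselling in that call; at 48 h, CG should likewise answer before the brief advice.
- Derive quit attempts, duration and continuous abstinence for the between-arm comparison only from the shared calls, with the look-back running from the previous shared call in both arms.
- State whether the 9-month call records the primary variable, and align the first hypothesis with the CO schedule at 48 h.
- Reconcile the blinding statement with the nurses' advice that patients tell their psychiatrist or psychologist, and state that callers are not blinded.

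The cost is a shared form, an analysis rule and a few extra minutes per IG call; no new type of staff is needed. The extra IG recordings would go unused in the between-arm comparison, though they remain available for describing the intervention.

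A shared script still leaves the nurse as assessor in IG. Having the assistants already trained for CG ask the questions in both arms would go further, at the price of additional call time for them.
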